### Criteria for the Termination of the Trial

The premature or scheduled termination of the trial will be executed immediately by the principal investigators, in absolute coordination with the IEC upon meeting any of the predefined criteria described in the following sections.

#### Expected Completion

The trial will be naturally terminated once the targeted sample size of 53 healthy volunteers has successfully completed the *Śodhana* protocol along with all corresponding baseline and postintervention laboratory evaluations.

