#### Population-Level Summary Measure

The mean intra-individual change score (mean delta difference) will be calculated from baseline to postintervention across the pooled cohort of 53 participants.

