#### Handling of Intercurrent Events

Intercurrent events anticipated in this protocol include clinical dropout, voluntary withdrawal, or protocol nonadherence (such as violating the inpatient *Ahara* or *Vihara* constraints). To handle these events, a “While-On-Treatment” strategy will be used. The target estimation focuses strictly on the biological treatment effect achieved while participants successfully adhere to the intensive inpatient intervention. Data points collected up to the exact moment of any protocol violation or withdrawal will be retained, while missing postevent endpoints will be mathematically handled using multiple imputation methods within our multivariable regression models, preventing bias from complete-case attrition.

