### Sample Size

The sample size is feasibility-driven. It was chosen based on pragmatic constraints. As this is an exploratory study, the goal is not to achieve definitive statistical power but to establish a foundation for future, larger-scale confirmatory research. Analyzing the census of Kerala, only 30% of the population could be sampled as healthy volunteers excluding NCDs, infectious diseases, other systemic illness like cancer, and age. The sample size was calculated as 53 using the following formula;

$$n=\frac{Z_{1-\alpha /2}^{2}\times P(1-P)}{d^{2}}$$

where Z_1-α/2_=1.96 (assuming a 95% CI), *P*=.5 (expected effeciency/anticipated proportion), and d=0.15 (15% margin of error), assuming a dropout rate of 20%.

Although this sample size is rooted in regional screening feasibility, a retrospective sensitivity power analysis confirmed that a finalized cohort of 53 individuals provides 80% statistical power (*α*=.05) to detect a small-to-medium intra-individual effect size (Cohen *d*=0.395) using a 2-sided paired samples framework. This standard biostatistical validation confirmed that, although the enrollment target is grounded in regional fieldwork constraints, it remains mathematically sensitive enough to capture subtle, homeostatic optimization trends in continuous aging biomarkers (MDA, SOD, and telomerase activity) within a healthy cohort.

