## Results

The study started recruiting participants in March 2025, and, as of April 4, 2025, 27 participants had voluntarily participated in *Vasantha Vamana*. The data analysis is pending. We expect to reach the targeted number of participants by December 2026. The data analysis will be conducted, and the results will be submitted for publication within the 6 months following study completion.

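### The trial ends at 53 completers, yet 53 was derived as an enrolment number that already allows for dropout, so the analysed cohort and the last post samples are left undefined

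*Protocol article*

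**What the plan says.** The end of the trial is set under Criteria for the Termination of the Trial. The opening sentence reads "The premature or scheduled termination of the trial will be executed immediately by the principal investigators", in coordination with the ethics committee, once a listed criterion is met. The first criterion, Expected Completion, reads "The trial will be naturally terminated once the targeted sample size of 53 healthy volunteers has successfully completed the" course, and it adds that each of these people must have a baseline and a post sample. The count is therefore of people with a finished course and both samples.

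The Sample Size section obtains 53 from a single-proportion precision formula with Z = 1.96 and P = 0.5. The remaining inputs are "d=0.15 (15% margin of error), assuming a dropout rate of 20" percent. It then treats the same 53 as a final cohort with 80% power at d = 0.395. Primary Purpose and the section on enrolment promotion also use 53 as the recruitment target.

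Under Population-Level Summary Measure the mean change is taken "across the pooled cohort of 53 participants", and Statistical Measures fits its regression to an entire cohort of 53. Handling of Intercurrent Events says that multiple imputation is used, "preventing bias from complete-case attrition". The missing-data and sensitivity sections compare an available-case analysis with baseline observation carried forward (BOCF). If both agree on significance, Sensitivity Analyses will call the findings stable and clear of attrition bias.

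Participant Retention and Discontinuation Protocols keeps the baseline values and exit reasons of people who stop and reports the reasons in the flow diagram.

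**The concern.** One number does three jobs: a dropout-inflated enrolment target, a count of completers that triggers the end, and the size of the analysed cohort. These agree only if nobody stops.

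If the termination rule is followed as written, a person who stops does not count and enrolment continues past that person. That is replacement in effect, although the protocol never says so. If the analysis is then run on the cohort of 53 named in the estimand, the set consists of finishers only. This is an uncontrolled pre-post study, and BOCF is its stated check against attrition. On a set of finishers that check cannot disagree with the main analysis on account of people who stopped, yet its agreement would be reported as evidence of no attrition bias.

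A second consequence comes from making scheduled termination immediate. The course lasts 18 to 20 days. No section says that people already in the course when the 53rd volunteer finishes will still have their T1 sample taken and analysed.

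**Working it through.** **Inputs.** Z = 1.96, P = 0.5, d = 0.15, dropout 20%, target 53, and 80% power at d = 0.395 (two-sided paired test, α = .05), all from Sample Size. Missing data below 5%, from Statistical Handling of Missing Data; 5% is used here as the low end for loss, which is an assumption. Course of 18 to 20 days, from the Abstract.

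**1. Reproduce the sample size.** n = Z²P(1−P)/d² = 1.96² × 0.25/0.15² = 42.68, or 43. Allowing for dropout, 42.68/0.80 = 53.36. Rounding up would give 54, so 53 reproduces apart from rounding. It is an enrolment number, with about 43 expected to finish.

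**2. Reproduce the power.** A paired t test (noncentral t, n − 1 degrees of freedom) with 53 pairs has 80.6% power at d = 0.395. The stated 80% reproduces, but only with 53 complete pairs.

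**3. The two meanings of 53.**

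| 53 means | Loss | Starters | Complete pairs | Power at d = 0.395 | d detectable at 80% power |
|---|---|---|---|---|---|
| Completers | 5% | 53/0.95 = 55.8, so 56 | 53 | 80.6% | 0.392 |
| Completers | 20% | 53/0.80 = 66.25, so 67 | 53 | 80.6% | 0.392 |
| Enrolled | 5% | 53 | 53 × 0.95 = 50.35, about 50 | 78.2% | 0.404 |
| Enrolled | 20% | 53 | 53 × 0.80 = 42.4, about 42 | 70.5% | 0.443 |

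With 43 pairs, the figure from the formula before inflation, power is 71.6%.

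**4. Effect on the BOCF check.** A stopper counted at zero change pulls the mean change down by the loss fraction. Over all starters the mean is 53/55.8 = 0.95 of the finishers' mean at 5% loss and 53/66.25 = 0.80 at 20%. Over the 53 finishers alone the factor is 53/53 = 1, because every member has a T1 by the definition in Expected Completion.

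**5. People in the course at the end.** The Results section says "as of April 4, 2025, 27 participants had voluntarily participated in" the spring procedure, recruitment having begun in March. With 18 to 20 day stays, overlapping courses are likely. How many would lack a T1 when the 53rd finishes depends on entry dates and on when enrolment closes. The protocol gives neither, so the number cannot be computed.

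**The case against.** The strongest reply is that the protocol does not describe the harm. No section says that people who stop are replaced. Sample Size builds dropout into 53 and calls it an enrolment target. If that governs, the cohort of 53 already contains the stoppers and BOCF has people to act on. The retention section keeps their data, and neither missing-data section limits BOCF to finishers. The rescue-event proportion under Core Outcome Set and Summary Measures is not tied to 53. Expected Completion describes an ordinary end, coordinated with the ethics committee; if enrolment closes in time, nobody need be in mid-course. The primary analysis uses complete pairs in any case, so rewording the stopping count would not remove selection on finishing.

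Most of this stands. A reader might infer that stoppers are replaced and deleted, or that a sizeable group will be cut off before T1. The documents do not support either: replacement is only implied, stoppers are retained, and the number in mid-course is unknown.

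The reply does not remove the conflict. It relies on 53 meaning enrolled, while Expected Completion plainly counts completers. On that reading the 80% power statement fails at the protocol's own 20% dropout. On the other reading the estimand's cohort of 53 leaves the stoppers out.

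**Conclusion.** The point holds as a conflict over what 53 counts, together with a termination rule that leaves the last T1 samples unprotected. It is not shown that anyone's data will be deleted.

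If 53 means completers, expect about 56 to 67 starters (5% to 20% loss), and the cohort described in the estimand and the regression is a subset of them. If 53 means enrolled, expect about 42 to 43 pairs at the stated dropout and about 71% power at d = 0.395.

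The attrition check is empty with respect to stoppers only if the analysed set is the 53 finishers, a reading the text permits but does not impose. The figures assume that the dropout and missing-data rates in the protocol apply to loss of T1. Recruitment is described as continuing, so the wording can still be settled before the cohort closes.

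**What to change.** 1. **Criteria for the Termination of the Trial:** confine immediate execution to premature termination.
2. **Expected Completion:** for example, *Enrolment closes when [stated number] participants have been enrolled. Everyone still in the course at that point is followed to the T1 sample and analysed, even if the number of pairs exceeds 53. The trial ends with the last participant's T1.*
3. **Population-Level Summary Measure, Expected Completion, Sample Size and Statistical Measures:** state in the same words whether 53 is enrolled or completed, and whether people who stop are replaced. If completed, give the larger enrolment number. If enrolled, restate the power for about 42 to 43 pairs.
4. **Missing-data, sensitivity and summary-measure sections:** name all participants who started as the set for BOCF and as the denominator for rescue and adherence proportions, and report the number started.

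None of this alters how or when an individual's treatment is stopped. The cost is wording, an ethics notification and possibly a few extra T1 assays. If 53 means enrolled, the stated power also becomes less favourable.

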#### Early Statistical Endpoints

The study may be halted prematurely if an early boundary condition is met, such as reaching a definitive positive or negative statistical endpoint sooner than anticipated during final data monitoring.

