## Methods

### Trial Design

This open-label, exploratory clinical trial consists of a single group and a primary endpoint of decreasing serum MDA values and increasing serum SOD values within 18 days to 20 days after *Vamana* in *Vasantha ritu* and *Virechana* in *Sarad ritu*. The participants will be recruited by the principal investigator consecutively by season: *Vamana* cohort in the *Vasantha ritu* (spring season) and *Virechana* cohort in the *Sarad ritu* (autumn season). Each participant is enrolled into only one seasonal arm based strictly on their chronological window of voluntary registration. There is no active assignment of participants; instead allocation follows a participant-driven, self-selection framework. The total study duration is 3 years. The study is registered in the Clinical Trial Registry-India (CTRI; CTRI/2024/02/062176).

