#### Futility Determination

The study will be terminated early if a midpoint clinical review or administrative audit leads to a clear determination that no statistically significant or clinically viable result can be obtained due to structural protocol constraints or unanticipated sample anomalies.

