#### Data Monitoring and Oversight Framework

This protocol is conducted as a single-center, investigator-initiated doctoral (PhD) research study in which the primary PhD scholar serves directly as the principal investigator. A separate, independent Data Monitoring Committee (DMC) is not required nor utilized. The trial evaluates standardized, time-tested institutional clinical procedures (*Vamana* and *Virechana*) that possess an established clinical safety track record, introducing minimal risk to participants. Instead of an external DMC, comprehensive scientific and data monitoring is executed directly by the candidate’s Doctoral Thesis Advisory Committee, which provides continuous academic and methodological oversight. Furthermore, participant safety monitoring, adverse event tracking, and ethical compliance are supervised directly by the IEC through scheduled periodic progress reports, with day-to-day data verification managed closely by the PhD scholar in her capacity as the principal investigator.

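### The protocol permits a premature halt on a statistical result without a boundary, a look schedule or alpha control, while its power and tests assume one fixed analysis of 53

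*Protocol article*

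**What the plan says.** The protocol article's section Criteria for the Termination of the Trial says the trial will be ended "upon meeting any of the predefined criteria described in the following sections". Two of those criteria mention a statistical result.

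- **Early Statistical Endpoints:** the trial "may be halted prematurely if an early boundary condition is met, such as reaching a definitive positive or negative statistical endpoint" and, in the same sentence, "sooner than anticipated during final data monitoring".
- **Futility Determination:** the protocol provides for early termination when a "midpoint clinical review or administrative audit leads to a clear determination that no statistically significant or clinically viable result can be obtained". The clause then limits the grounds for such a finding, which must be "due to structural protocol constraints or unanticipated sample anomalies".

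Other sections bear on these:

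- Sample Size computes 80% power at Cohen d=0.395 for a two-sided paired test of 53 at alpha .05. It makes no allowance for an interim look.
- Statistical Measures applies P<.05 without adjustment. Primary Outcome asks for P<.05 together with a moderate to large Cohen d, and Statistical Measures sets medium at 0.5.
- Data Monitoring and Oversight Framework: "A separate, independent Data Monitoring Committee (DMC) is not required nor utilized".
- Trial Design: "The participants will be recruited by the principal investigator consecutively by season", with Vamana in spring and Virechana in autumn. Results reports that "as of April 4, 2025, 27 participants had voluntarily participated in" the spring Vamana programme.
- Primary Objective names both procedures, and Population-Level Summary Measure pools all 53 participants.
- Future Directions intends the data to supply standard deviations and accurate effect sizes for a later randomised trial.

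**The concern.** A rule that lets a trial end because the accumulating result looks good gives that result extra chances to cross the line, unless the threshold at each look is adjusted. This protocol authorises such a stop and calls its criteria predefined, but the design around it is that of a trial analysed once. The wording does not settle when the stop could happen: a halt cannot be premature and also belong to final data monitoring.

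Three things are at stake. The first is the false-positive rate behind the claim of reduced oxidative stress. The second is the effect size, which a favourable early stop pushes upward and which the next trial is to be planned on. The third is coverage of both procedures, because enrolment follows the seasons. The trial is open-label, and the principal investigator collects the assay results and records them in the case report form (Data Collection Personnel and Process). The data are therefore within reach of those who can stop the trial.

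**Working it through.** **Inputs from the protocol:** N=53, two-sided alpha .05, paired test, d=0.395 (Sample Size); 27 participants by April 4, 2025, all Vamana (Results); medium Cohen d=0.5 (Statistical Measures).

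**Assumption:** the number and timing of looks are not given. The base case is one look at n=27, which is 27/53 = 50.9% of target, plus the final test at n=53.

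**1. The plan's own figures.**
- Sample size: 1.96² × 0.5 × 0.5 / 0.15² = 42.68; allowing for 20% dropout, 42.68 / 0.8 = 53.36, reported as 53.
- Power: the noncentral t with n=53 and d=0.395 gives 80.6%, against the stated 80%.
- Both are reproduced, and both are for a single analysis.

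**2. Stop triggered by P<.05 alone.** The two test statistics have correlation √(27/53) = 0.714. The chance under the null that either exceeds 1.96 in absolute value is 8.3% (bivariate normal; simulated paired t tests agree), against 5.0% for one final test. In the favourable direction only, 2.5% becomes 4.2%. With more equally spaced looks, purely as a range, the two-sided figure is 10.8% for three in total, 12.7% for four and 14.4% for five.

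**3. Stop triggered by the joint criterion, P<.05 and |d| ≥ 0.5.** For a paired test t = d√n.
- At n=27: t ≥ 0.5 × √27 = 2.60, two-sided P = .0152.
- At n=53: t ≥ 0.5 × √53 = 3.64, two-sided P = .0006.
- At both sizes the d condition is the stricter one. A single final test therefore has type I error of 0.06 to 0.07%.
- With both looks the error lies between 1.52% (first look alone) and 1.52% + 0.06% = 1.58%, so about 1.5%.

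**4. Effect size.** At n=27 the two-sided critical t is 2.056, so P<.05 requires an observed |d| of at least 2.056 / √27 = 0.396. The joint criterion requires at least 0.5. A favourable stop at that look can only report estimates above these values, and smaller ones are carried forward. This selection biases the reported effect upward under either criterion.

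**5. Sensitivity of an analysis at n=27.** Power at d=0.395 is 51%, and 80% power needs d=0.56. A negative conclusion drawn there would miss the protocol's own target effect about half the time.

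**6. Composition.** At 27 of 53 as reported in April 2025 there are 27 Vamana and 0 Virechana participants. The pooled estimand and the between-cohort ANCOVA in Statistical Measures both need the second group.

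**7. Futility clause.** Stopping only for lack of promise does not raise type I error. With an illustrative rule of stopping at n=27 when |t| < 0.5, simulated error moves from 5.1% to 4.9%.

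**The case against.** The best defence is that the study is exploratory and says it does not seek definitive power. The stop is permissive, any termination is coordinated with the ethics committee, the Doctoral Thesis Advisory Committee oversees the data, and laboratory staff are blinded to time point. Results places data analysis after study completion, which suggests one final analysis. A boundary might also stand in an analysis plan that is not shown.

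This lowers the stakes but does not remove the problem. The termination section says its criteria are described there, and what it describes is permission to stop on a statistical result. Primary Outcome still uses P<.05 as part of its test of success. If one final analysis is intended, the clause contradicts it.

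Several stronger readings are tempting, and the documents do not support them.

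- **The error rate is 8% or more.** That holds only if P<.05 alone triggers the stop. Under the joint criterion with one look it is about 1.5%.
- **There will be four or six looks.** Nothing says so. Trial Monitoring Processes gives the six-monthly committee meetings the tasks of auditing progress, consent records and compliance, and mentions no outcome testing.
- **The error is about 16% across MDA and SOD.** That figure assumes independent endpoints, either of which could trigger the stop. Of it, 9.7% is two-endpoint multiplicity that exists with no interim look.
- **The futility clause inflates false positives.** It does not, and its stated grounds are structural constraints or sample anomalies.
- **A midpoint stop would leave only Vamana.** The midpoint is undefined and is named only in the futility clause. A calendar midpoint could fall after an autumn season.

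**Conclusion.** The point holds for the Early Statistical Endpoints clause. It authorises a premature stop on a favourable or unfavourable statistical result without the terms that would make it a rule. It conflicts with the single fixed analysis used elsewhere and contradicts itself on timing.

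The effect on type I error depends on what the clause means by a definitive result. For one assumed look at n=27 plus the final test it is 8.3% per endpoint on P<.05 alone, and about 1.5% on the joint criterion. The upward bias in the effect size does not depend on that choice, and it works against the planning use stated in Future Directions. The loss of power to about 51% rests on an analysis at n=27. The absence of Virechana data rests further on a stop at half of target enrolment with the composition reported in April 2025.

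**What to change.** Delete the Early Statistical Endpoints criterion. State that MDA, SOD and telomerase activity are each tested once, after both seasonal cohorts have completed post-intervention sampling. This restores 5% per endpoint for the single P<.05 test.

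If a statistical stop is to be kept, state when the look occurs, which endpoint it concerns and a boundary that controls alpha. For one look at 27 of 53, two that hold the two-sided level at .05 are:

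- O'Brien-Fleming type: nominal P<.0056 at the look and P<.0479 at the end.
- Pocock type: P<.0295 at both.

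In that case also resolve the conflict between a premature halt and final data monitoring, and say how a look before the second seasonal cohort would serve the pooled estimand.

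In Futility Determination, remove the reference to statistical significance, so that termination there rests on feasibility and not on an interim significance result. Leave the safety and administrative criteria as they are.

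The cost is a wording change and notification of the ethics committee. Little is lost, since each participant is in the trial for 18 to 20 days and the total is 53.

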#### Serious Adverse Reactions

The trial will be shut down immediately if any participant experiences serious adverse reactions, including severe abnormalities in vital signs (eg, severe cardiovascular instability), persistent biological distress, or unexpected toxicological outcomes.

